## Study Assessments

### Efficacy Assessments

Efficacy assessments consist of serum HCV-RNA via PCR and ALT determination.

Quantitative viral titers (COBAS TaqMan 48™)) will be obtained during screening, day 28, week 12, week 24, End-of-Treatment, and 24 weeks post-end of treatment and sent to local lab for assessment.

Patients who discontinue from treatment prematurely, are expected to return for sampling for HCV RNA at end-of-treatment, and 24 weeks post-end of treatment.

###### Viral Kinetic

Quantitative viral titers (COBAS TaqMan 48™) will be obtained at screening, day 0, day 3, day 7, day 28, week 12, End-of-Treatment, and 24 weeks post-end of treatment and sent to central lab for analysis. Group B (“Priming”) will also obtain a plasma sample on day -28 (before the first “priming” dose of ribavirin) for analysis at the central lab.

Instructions for sampling and shipment can be found in Appendix.

**Ribavirin Plasma Concentration**

Trough plasma concentrations of ribavirin will be obtained before the morning dose of ribavirin day 1, day 3, day 7, day, 14, day 28, week 8, week 12, week 18, End-of-Treatment. Group B (“Priming”) will also obtain trough plasma sample for ribavirin day -27 (the first day after initiation of “priming” dose of ribavirin) and day -21 (one week after initiation of “priming” dose of ribavirin).

Instructions for sampling and shipment can be found in Appendix.

**IP-10**

During screening and on days 0, 1, 3, 7, and 14, and weeks 8, 18, and 24 plasma will be drawn for later evaluation of IP-10 concentrations.

**IL-28B Polymorfism**

During the screening visit an EDTA blod sample will be drawn for later evaluation of IL-28B polymorfism and the impact on outcome.

**Vitamin D**

During the screening period a serum sample will be drawn for later analysis of Vitamin D (25 hydroxy-vitamin D) at a central laboratory.

###### Liver biopsy (if obtained)

Four or more unstained slides of and/or paraffin embedded liver biopsies (archived or taken during screening) are together with the local pathologist evaluation sent to Sahlgrenska University Hospital, Gothenburg, Sweden for assessment.

If a liver biopsy is obtained during the screening period, it is encouraged that 1 cm liver tissue be placed in Allprotect Tissue Reagent (Qiagen cat. No. 76405) and immediately frozen at -70°C for later evaluation of the predictive value of quantifying mRNA expression for IFI-27, IP-10, CXXL-6, IL-2, IL-8, IL-10, -IFN, TNF-, KRT19, COL1A1, MMP7, TIMP1, FASL, AIF1 for determining which patients will obtain a sustained virological response (SVR) when treated with peginterferon alfa-2 and ribavirin combination therapy.

Instructions for sampling and shipment can be found in Appendix

**FibroScan (optional)**

FibroSacn evaluations are optional but encouraged during the screening period as well as week 24 after completion of therapy.

**PBMCs during screening (optional)**

If possible sampling for PBMC’s during screening is encouraged in order to evaluate the predictive value of monitoring CD56 negative NK, CD4+ CD38+, CD8+ CD38+, CD8+CD16+, Foxp3+, and pDC (CD303+) cells in peripheral blood and liver biopsies as analyzed by FACS prior to and after the initiation of therapy for determining which patients will obtain a sustained virological response (SVR) when treated with peginterferon alfa-2 and ribavirin combination therapy.

Instructions for sampling and shipment can be found in Appendix

### Safety Assessments

Safety assessments will be performed throughout the treatment period and the follow-up period as outlined in the Schedule of Assessments (Section 5.1). Measures of safety will consist of:

- Vital signs consisting of systolic and diastolic blood pressure, heart rate, and body weight
- Clinical chemistry including AST, gamma-GT, total bilirubin, alkaline phosphatase, albumin, creatinine, and uric acid
- Serum ALT activities at each visit
- Hematology including complete (hemoglobin, reticulocytes, WBC, platelets) and differential blood count
- Urinalysis consisting of protein, blood, and glucose examinations
- Thyroid function test
- Women of child-bearing potential need to have a urine or serum **pregnancy test** (a) within 24 hours prior to first dose (all female patients) (b) every study visit while on test drug therapy and (c) for 24 weeks following the last dose of test medication. Investigators must ensure that any patient who is discontinued from study medication prematurely has the follow-up pregnancy tests performed for the full 24 weeks following the last dose of study medication.
- Ophthalmologic examination: Patients with preexisting ophthalmologic disorders (e.g. diabetic or hypertensive retinopathy) should receive periodic ophthalmologic exams during therapy. Pegylated interferon treatment should be discontinued in patients who develop new or worsening ophthalmologic disorders. Any patient complaining of decrease or loss of vision must have an eye examination
- Documentation of concomitant medication
- Documentation of dose adjustments and premature withdrawals for safety reasons or intolerance.
- Documentation of clinical adverse events (AEs).
- An independent DSMB will evaluate safety after the first 30 patients have reached treatment weeks 2 and 12.
- The use of erythropoietin (NeoRecormon) ≥3000 IE 3 times week sc is permitted throughout the study at the discretion of the treating physician with the exception if the patient has any of the following exclusion criteria for the use of erythropoietin: platelet count >500,000, risk of thrombosis, or poorly controlled hypertension, especially if hemoglobin decreases persistently to < 10.0 g/dL or in the event of a rapid decrease in hemoglobin exceeding 4.0 g/dL over a 2 week period. If erythropoietin is initiated, a new ribavirin concentration at local lab should be evaluated after 4 weeks in Groups A (“Loading”) and B (“Priming”).
- In the event of anemia, dose reductions of ribavirin are permitted in all study arms throughout the study at the discretion of the treating physician.
- If hemoglobin decreases to < 8.0 g/dL, ribavirin should be discontinued.
- If hemoglobin decreases to < 7.0 g/dL, blood transfusion should be considered at the discretion of the treating physician.
- If hemoglobin decreases to < 6.5 g/dL, blood transfusion should be given.
- Patients will discontinue therapy if the decrease in plasma HCV RNA between week 12 and baseline is ≤ 2 log10 IU/mL or if plasma HCV RNA is still detectable by treatment week 24.
- The members of the Steering Committee in each respective country will be responsible for monitoring the participating centers in their country. One or more experienced monitor is recommended per participating country.
- Only experienced treatment centers willing to include ≥ 5 patients will be permitted to participate in the study.
- All serious adverse events in the study will be reported to IST and Welwyn.

Patients will also be assessed for safety after their last dose of test medication following premature discontinuation from the study. This includes a laboratory evaluation at least 12 weeks following the final dose of test drug (for details please refer to section 3.1). Generally patients should be encouraged to stay in the trial. Counseling about contraception and behaviors associated with an increased risk of pregnancy must be repeated on a monthly basis.

# end points of the study

## Primary Endpoint

The early virological response as measures by the decline in HCV-RNA during the first 12 weeks (in particular the first and second phase decline) of peginterferon alpha-2a and ribavirin therapy in the three study arms.

## Secondary Efficacy Endpoints

## Percentage of patients with non-detectable HCV-RNA at end the end of 24 week or 48 week of treatment as measured by Roche COBAS TaqMan

## VRVR, RVR, cEVR, and pEVR rates defined as percentage of patients achieving these goals as measured by TaqMan PCR in the three study arms.

## Percentage of patients with non-detectable HCV-RNA at study day 1, 3, 7, 14, 21, 28, week 8, week 12, end of treatment, and 24 weeks after completion of treatment as measured by TaqMan PCR as compared to day 0.

## SVR rate defined as percentage of patients with non-detectable HCV-RNA as measured by TaqMan PCR at 24 weeks post completion of the treatment period in the three study arms.

## Relapse rates defined as percentage of patients with non-detectable HCV-RNA as measured by TaqMan PCR at the end-of-treatment but with detectable HCV-RNA 24 weeks post completion of the treatment period in the three study arms.

## SVR rate and percentage of patients with normal serum ALT levels at 24 weeks after completion of the treatment period in the total patient population, and its association with the following factors:

## early virological response

## pharmacokinetic response to ribavirin

# STUDY MEDICATIONS

## Dose and Schedule of Study Medications

Patients will receive PEGASYS® 180 g in 0.5 mL (prefilled syringes) administered sc once weekly. Specific guidelines for adjusting the dose of PEGASYS® are provided in Section 8.3. All PEGASYS® administrations will be via the sc route utilizing sterile technique. Test drug may be self-administered by the patients, except for the first dose, which should be administered in the clinic under the supervision of study personnel. Before providing the patient with test medication, the investigator or a qualified staff member will instruct the patient on the proper methods of storage of the medication, self-injection, and management and disposal of needles and syringes.

Patients will in combination with PEGASYS receive COPEGUS (ribavirin) which is administered p.o. daily: 13 mg/kg body weight. In Group A, patients will receive COPEGUS (ribavirin) 26 mg/kg body weight for the first 2 weeks (“Loading”) followed by COPEGUS (ribavirin) 13 mg/kg body weight for the remaining treatment duration. In Group B, patients will receive monotherapy with COPEGUS (ribavirin) 13 mg/kg body weight for 4 weeks prior to initiation of PEGASYS combination therapy. In both Group A and B, a ribavirin concentration will be obtained at local lab on day 28 after the initiation of PEGASYS, allowing for dose adjustments as deemed fit by the treating physician with the goal of achieving a ribavirin concentration (≥ 2.5 mg/L or 10.25 μmol/L). In Group C all patients will receive COPEGUS (ribavirin) 13 mg/kg body weight in combination with PEGASYS for the entire treatment duration without a ribavirin concentration without assessment on day 28 (“Standard-of-Care”)

All patients in this study will receive ribavirin treatment with food. By definition, ribavirin, with food entails taking their doses within 1 hour before or 2 hours after a meal. The meal should be considered “regular” as opposed to “fat-restricted”. Dose adjustment guidelines for ribavirin are provided in section 8.3.

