| OBJECTIVES | Primary   - To demonstrate the efficacy of (A) 2 weeks of high dose of ribavirin (“loading”, ≥26 mg/kg/day for 14 days followed by ≥13 mg/kg/day) followed by concentration targeted (≥ 2.5 mg/L (10.25 μmol/L) 28 days after initiation of ribavirin therapy) dosing of ribavirin vs. (B) 4 weeks of ribavirin dosing before initiation of PEG-interferon dosing (“priming”, ≥13 mg/kg/day) followed by concentration targeted (≥ 2.5 mg/L (10.25 μmol/L) 28 days after initiation of ribavirin therapy) dosing of ribavirin in combination with peginterferon alpha-2a in interferon naïve patients with chronic hepatitis C (CHC) virus genotype 1 infection as compared to (C) standard-of-care dosing of ribavirin (≥13 mg/kg/day without monitoring of ribavirin concentrations) in combination with peginterferon alpha-2a as evaluated by the early viral kinetic response measured by effect on the initial decline of HCV-RNA (during the first days after initiating peginterferon and ribavirin therapy) and second phase decline (day 7 to week 12 of therapy).   Secondary  To prospectively evaluate:   - the efficacy of 2 week loading or 4 week priming followed by concentration targeted dosing of ribavirin in combination with peginterferon alpha-2a in interferon naïve patients with chronic hepatitis C (CHC) virus genotype 1 infection as compared to standard-of-care dosing of ribavirin in combination with peginterferon alpha-2a as evaluated by the proportion of patients achieving VRVR ( “very rapid virologic response” i.e. HCV-RNA below 1000 U/mL at treatment day 7 after intiation of PEG-interferon), RVR (“rapid virologic response”, undetectable HCV-RNA at treatment day 28 after intiation of PEG-interferon), cEVR (“complete early virologic response”, i.e. undetectable HCV-RNA at treatment week 12 after intiation of PEG-interferon), and pEVR (“partial early virologic response”, i.e. decline of HCV-RNA by at least 2 log10 compared with baseline at treatment week 12 after intiation of PEG-interferon). - the efficacy of 2 week loading or 4 week priming followed by concentration targeted dosing of ribavirin in combination with peginterferon alpha-2a in interferon naïve patients with chronic hepatitis C (CHC) virus genotype 1 infection is superior to standard-of-care dosing of ribavirin, peginterferon alpha-2a therapy as evaluated by sustained virological response (SVR, undetectable HCV-RNA 24 weeks after end of treatment). - the predictive value of monitoring of viral load at day 0 (before the 1st dose of peginterferon alpha-2a), day 3, day 7 (before the 2nd dose of peginterferon alpha-2a), and day 28 (before the 5th dose of peginterferon alpha-2a) determining which patients will obtain a sustained virological response (SVR) when treated with ribavirin and peginterferon alpha-2a therapy. - the association between the trough concentrations of ribavirin (day 1, day 3, day 7, day 14, day 28, week 8, week 12, week 18, and end-of-treatment), and the therapeutic efficacy of ribavirin and peginterferon alpha-2a therapy. - The association between plasma IP-10 (days 0, 1, 3, 7, and 14, and weeks 8, 18, and 24), and the therapeutic efficacy of ribavirin and peginterferon alpha-2a therapy. - the effect of IL-28B ploymorfism on the viral kinetic response. - the effect of baseline vitamin D concentrations on the viral kinetic response. - the effect of baseline IP-10 concentrations on the viral kinetic response. - the association between liver histology as evaluated by the Ishak scoring system (modified HAI score) and steatosis grading if a liver biopsy has been performed, and the therapeutic efficacy of peginterferon alfa-2 combination therapy with ribavirin. - the association between liver stiffness as evaluated by the FibroScan if this has been performed and the therapeutic efficacy of peginterferon alfa-2 combination therapy with ribavirin. - the association between liver fibrosis as evaluated by the GUCI and APRI indexes as well as hyaluronic acid, and the therapeutic efficacy of peginterferon alfa-2 combination therapy with ribavirin. - the association between body mass index (BMI), waist circumference, weight and age, and the therapeutic efficacy of peginterferon alfa-2 combination therapy with ribavirin. - the predictive value of monitoring CD56 negative NK, CD4+ CD38+, CD8+ CD38+, CD8+CD16+, Foxp3+, and pDC (CD303+) cells in peripheral blood and liver biopsies as analyzed by FACS prior to and after the initiation of therapy for determining which patients will obtain a sustained virological response (SVR) when treated with peginterferon alfa-2 and ribavirin combination therapy. - the predictive value of quantifying mRNA expression in pre-treatment liver biopsies for IFI-27, IP-10, CXXL-6, IL-2, IL-8, IL-10, -IFN, TNF-, KRT19, COL1A1, MMP7, TIMP1, FASL, AIF1 for determining which patients will obtain a sustained virological response (SVR) when treated with peginterferon alfa-2 and ribavirin combination therapy.   Others:  To prospectively evaluate:   - the predictive value of monitoring the trough concentrations of ribavirin (day 1, day 3, day 7), and the final steady-state concentration of ribavirin.. - the safety of peginterferon alpha-2a combination therapy with concentration targeted dosing of ribavirin in combination peginterferon alpha-2a, based on accumulated number of adverse events and severe adverse events as well as the impact on quality of life during treatment and follow-up phase. - the safety of peginterferon alpha-2a combination therapy with concentration targeted dosing of ribavirin in combination peginterferon alpha-2a, with particular regards to the number of patients in each treatment arm developing anemia grade 1 (10.5-9.5 g/dL), grade 2 (9.4-8.0 g/dL), grade 3 (7.9-6.5 g/dL), and grade 4 (<6.5 g/dL). | | |

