| LENGTH OF STUDY | Period of enrollment: 52 weeks | | |
| Group A (“Loading”): PEG-IFN α-2a 180 g/week plus loading (≥26 mg/kg/day for 2 weeks followed by ≥13 mg/kg/day) and concentration targeted (≥ 2.5 mg/L, i.e ≥ 10.25 mol/L, as measured after 4 weeks of therapy) dosing of ribavirin and response guided treatment duration (RVR 24 weeks, non-RVR 48 weeks, pEVR consider 72 weeks), follow-up period 24 weeks | | |
| Group B (“Priming”): Standard-of-care dosing of ribavirin (≥13 mg/kg/day) without PEG-IFN for 4 weeks followed by 24-48 additional weeks of PEG-IFN α-2a 180 g/week plus standard-of-care dosing of ribavirin (≥13 mg/kg/day) and concentration targeted (≥ 2.5 mg/L, i.e ≥ 10.25 mol/L, as measured after 28 days after the initiation of ribavirin) dosing of ribavirin and response guided treatment duration (RVR 28 weeks, non-RVR 52 weeks, pEVR consider 76 weeks), follow-up period 24 weeks  Group C (“Standard-of-Care”): PEG-IFN α-2a 180 g/week plus standard-of-care dosing of ribavirin (≥13 mg/kg/day without any measurement of ribavirin concentration) and response guided treatment duration (RVR 24 weeks, non-RVR 48 weeks, pEVR consider 72 weeks), follow-up period 24 weeks | | |
| DURATION OF STUDY | October 2010 till July 2013 including a recruitment period of 52 weeks, with an interim analysis of the primary study endpoints after all patients reached treatment 12 week. | | |
| INVESTIGATIONAL PRODUCT(S) DOSE/ ROUTE/ REGIMEN | Peginterferon α-2a  Copegus (ribavirin): 200-400 mg/tablet | | |
| ASSESSMENTS OF: |  | | |

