## Secondary Objectives

To prospectively evaluate:

- the efficacy of 2 week loading or 4 week priming followed by concentration targeted dosing of ribavirin in combination with peginterferon alpha-2a in interferon naïve patients with chronic hepatitis C (CHC) virus genotype 1 infection as compared to standard-of-care dosing of ribavirin in combination with peginterferon alpha-2a as evaluated by the proportion of patients achieving VRVR ( “very rapid virologic response” i.e. HCV-RNA below 1000 U/mL at treatment day 7 after intiation of PEG-interferon), RVR (“rapid virologic response”, undetectable HCV-RNA at treatment day 28 after intiation of PEG-interferon), cEVR (“complete early virologic response”, i.e. undetectable HCV-RNA at treatment week 12 after intiation of PEG-interferon), and pEVR (“partial early virologic response”, i.e. decline of HCV-RNA by at least 2 log10 compared with baseline at treatment week 12 after intiation of PEG-interferon).
- the efficacy of 2 week loading or 4 week priming followed by concentration targeted dosing of ribavirin in combination with peginterferon alpha-2a in interferon naïve patients with chronic hepatitis C (CHC) virus genotype 1 infection is superior to standard-of-care dosing of ribavirin, peginterferon alpha-2a therapy as evaluated by sustained virological response (SVR, undetectable HCV-RNA 24 weeks after end of treatment).
- the predictive value of monitoring of viral load at day 0 (before the 1st dose of peginterferon alpha-2a), day 3, day 7 (before the 2nd dose of peginterferon alpha-2a), and day 28 (before the 5th dose of peginterferon alpha-2a) for determining which patients will obtain a sustained virological response (SVR) when treated with ribavirin and peginterferon alpha-2a therapy.
- the association between the trough concentrations of ribavirin (day 1, day 3, day 7, day 28, week 8, week 12, week 16, and end-of-treatment), and the therapeutic efficacy of ribavirin and peginterferon alpha-2a therapy.
- The association between plasma IP-10 (days 0, 1, 3, 7, and 14, and weeks 8, 18, and 24), and the therapeutic efficacy of ribavirin and peginterferon alpha-2a therapy.
- the effect of IL-28B polymorfism on the viral kinetic response and SVR.
- the effect of baseline vitamin D concentrations on the viral kinetic response and SVR.

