# STUDY design

## Overview of Study Design and Dosing Regimen

This study will be conducted as a phase III, open label, multicenter trial. A total of 105 patients will be randomized to one of three possible treatment groups.

**Group A:** (“Loading”): PEG-IFN α-2a 180 g/week plus loading (≥26 mg/kg/day for 2 weeks followed by ≥13 mg/kg/day) and concentration targeted (≥ 2.5 mg/L (10.25 μmol/L) 28 days after initiation of ribavirin therapy) dosing of ribavirin and response guided treatment duration (RVR 24 weeks, non-RVR 48 weeks, pEVR consider 72 weeks), follow-up period 24 weeks.

**Group B**: (“Priming”): Standard-of-care dosing of ribavirin (≥13 mg/kg/day) without PEG-IFN for 4 weeks followed by 24-48 additional weeks of PEG-IFN α-2a 180 g/week plus standard-of-care dosing of ribavirin (≥13 mg/kg/day) and concentration targeted (≥ 2.5 mg/L (10.25 μmol/L) 28 days after initiation of ribavirin therapy) dosing of ribavirin and response guided treatment duration (RVR 28 weeks, non-RVR 52 weeks, pEVR consider 76 weeks), follow-up period 24 weeks.

**Group C:** (“Standard-of-Care”): PEG-IFN α-2a 180 g/week plus standard-of-care dosing of ribavirin (≥13 mg/kg/day without any measurement of ribavirin concentration) and response guided treatment duration (RVR 24 weeks, non-RVR 48 weeks, pEVR consider 72 weeks), follow-up period 24 weeks.

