**Appendix 3: COPEGUS Intended Dose and Dose Adjustment Guidelines**

| Group A: Intended Ribavirin Dosing | | |
| --- | --- | --- |
| Weight | Ribavirin dose day 0 – day 14* | Ribavirin dose day 15 -  End of Treatment** |
| 45-60 kg | 1600 mg | 800 mg |
| 61-75 kg | 2000 mg | 1000 mg |
| 76-90 kg | 2400 mg | 1200 mg |
| 91-105 kg | 2800 mg | 1400 mg |
| *Dose given TID. **Ribavirin concentration measured on treatment day 28. Dose | | |
| adjustments will be made at the discretion of the treating physician with the goal of | | |
| achieving ≥ 2.5 mg/L (10.25 μmol/L). A new ribavirin concentration is recommended | | |
| after an additional period of 4 weeks if the ribavirin dose is adjusted as above. | | |

| Group B and C: Intended Ribavirin Dosing |  |
| --- | --- |
| Weight | Ribavirin dose day 0 –  End of Treatment a,b |
| 45-60 kg | 800 mg |
| 61-75 kg | 1000 mg |
| 76-90 kg | 1200 mg |
| 91-105 kg | 1400 mg |
| aNo ribavirin concentrations will be measured while on treatment for group C.  bGroup B will receive 4 weeks of priming with ribavirin without PEG-IFN. | |

If the ribavirin concentration is below the target 2.5 mg/L (10.25 μmol/L) 28 days after the initiation of ribavirin, the dose of ribavirin should be increased as soon as possible preferably within 2 weeks of measuring the ribavirin concentration if the patient tolerates. The new recommended dose is the previously given dose divided by the concentration of ribavirin measured multiplied by the target concentration, i.e. 2.5 mg/L (10.25 μmol/L) as suggested in the table below. In the event of an increase in ribavirin dosing in Groups A (“Loading”) and B (“Priming”), a new local ribavirin concentration should be evaluated after 4 weeks.

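### Section 7.1 alone times the Group B local ribavirin level from PEGASYS start, 28 days later than the primary objective, the Group B regimen and Appendix 3, which time it from ribavirin start

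*Protocol*

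**What the plan says.** The local ribavirin level is what allows the dose to be raised towards 2.5 mg/L in Groups A and B. The protocol times it in several places.

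- **From PEGASYS start.** Section 7.1: "In both Group A and B, a ribavirin concentration will be obtained at local lab on day 28 after the initiation of PEGASYS".
- **From ribavirin start.** The primary objective, in the Synopsis and again in Section 2.1: "28 days after initiation of ribavirin therapy) dosing of ribavirin in combination with peginterferon alpha-2a". The Group B regimen in Section 3.1: "28 days after initiation of ribavirin therapy) dosing of ribavirin and response guided treatment duration (RVR 28 weeks". The Group B regimen in the Synopsis: "as measured after 28 days after the initiation of ribavirin". The dose-increase rule in Appendix 3, for a level below target: "28 days after the initiation of ribavirin, the dose of ribavirin should be increased as soon as possible".
- **No anchor stated.** Section 8.3.2 and the pharmacokinetics part of Appendix 5 say only day 28. Both refer the reader to Appendix 3 for the adjustment.

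Section 5.3.1 numbers the priming weeks of Group B in negative days. For HCV-RNA, Group B "will also obtain a plasma sample on day -28", and for ribavirin it "will also obtain trough plasma sample for ribavirin day -27 (the first day after initiation of" priming. Section 2.2 ties the viral-load day 28 to the interferon schedule: "and day 28 (before the 5th dose of peginterferon alpha-2a) for determining which patients will obtain a sustained virological response". The virology part of Appendix 5 describes day 0 both as just before the first pegylated interferon dose and as the day of the first dose of study medication.

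**The concern.** In Group A both drugs start together, so the two anchors give the same day. In Group B ribavirin starts 4 weeks before PEGASYS, so they give different days, and no sentence says which governs or describes two separate routine local levels.

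This is a dosing instruction to sites. The primary objective defines the Group B intervention as priming followed by targeting on a level taken 28 days after ribavirin starts. A site that works from Section 7.1 would obtain that level, and so begin targeting, 4 weeks later. The day 0 definition in Appendix 5 does not help, because in Group B the first interferon dose and the first dose of study medication are 28 days apart. In a multicentre trial, sites could deliver different versions of Group B without any of them departing from the text.

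**Working it through.** The check is day arithmetic on the protocol's own numbering. The protocol gives no figure to reproduce.

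**Inputs**

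- Group B ribavirin start: study day -28 (Section 5.3.1, Viral Kinetic; 4 weeks of priming in Section 3.1).
- PEGASYS start: study day 0.
- Preferred time to an increase after a low level: within 2 weeks (Section 8.3.2 and Appendix 3).
- Recheck: 4 weeks after a dose change (Section 8.3.2).
- Slope used for the sample size: days 7 to 28 (Section 9.3).
- RVR: read 28 days after the start of PEG-interferon (Section 2.2).
- Second-phase window of the primary objective: day 7 to week 12, that is day 7 to day 84 (Section 2.1).

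**Group B under each clock**

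| Event | Ribavirin clock | PEGASYS clock (Section 7.1) |
| --- | --- | --- |
| Local level, study day | -28 + 28 = 0 | 0 + 28 = 28 |
| Days of ribavirin at the level | 28 | 28 + 28 = 56 |
| Increase within 14 days | 0 to 14 | 28 to 42 |
| Recheck 28 days after the increase | 28 to 42 | 56 to 70 |

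The gap is 28 - 0 = 28 days.

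**Against the analysis windows**

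- Day 7 to 28 slope and RVR. On the ribavirin clock an increase can come before or during the slope and before RVR. On the PEGASYS clock the level is drawn on the day the slope ends and RVR is read, so no level-driven increase can precede either.
- Day 7 to week 12 window. An increase on days 28 to 42 still leaves 84 - 28 = 56 to 84 - 42 = 42 days of the window.
- Day 0 to 3 decline. Little affected on either clock, since the earliest level-driven increase is on day 0.

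**Which texts support which clock**

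Section 7.1 is the only express statement of the PEGASYS anchor for the local level. Section 8.3.2 and Appendix 5 do not state an anchor but lead to Appendix 3, which uses ribavirin start. The rationale in Section 1.4.1 says that a level after 4 weeks will be available in the priming arm, which also fits ribavirin start. The negative-day numbering and the tie of day 28 to the fifth interferon dose pull a bare day 28 towards the PEGASYS clock. Appendix 5 supports either reading of day 0.

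**The case against.** The strongest reply is that this is one stray phrase against a consistent rule. Section 7.1 itself refers dose adjustment to Section 8.3, which leads to Appendix 3, and Appendix 3 is clear. Much of this stands: the weight of the text is on the ribavirin clock, and that is why the correction is easy to choose. It does not remove the conflict, because Section 7.1 is the dosing section, names both groups and states its anchor in full.

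A reader might infer more than the protocol supports, in four ways.

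- *That Section 8.3.2 and Appendix 5 side with Section 7.1.* They give no anchor and point to Appendix 3, so they are ambiguous.
- *That no Group B level is scheduled at day 0.* The sampling list in Appendix 5 that lacks one is for the central laboratory, and Section 5.3.1 does not separate local from central samples. The Section 5.1 schedule table, which may settle the point, was not in the text available for this review.
- *That the later clock takes targeting out of the primary endpoint.* It does not. The primary second phase runs to week 12, and an increase on days 28 to 42 falls inside it.
- *That the SVR analysis by day 28 target attainment is wrongly specified.* Which sample counts as day 28 for Group B in that analysis can properly be left to the SAP.

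It is also fair to say that the practical effect may be small. Increases are recommended but not mandatory, and they depend on tolerance and the physician's judgement. Section 1.4.1 says that steady state takes more than 4 weeks, so even an increase on days 0 to 14 would be only partly reflected in plasma levels by day 28.

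**Conclusion.** The point holds as an internal contradiction in a dosing rule. Section 7.1 places the Group B local level 28 days later than the primary objective, the Group B regimen and Appendix 3 do, and nothing in the available text resolves it. It concerns Group B only, 35 of the 105 planned patients.

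The 35 is the size of the arm, not a count of patients affected. Only patients below target who tolerate an increase and are given one would be treated differently, and the protocol gives no basis for estimating their number. No size of effect on viral decline is claimed. What can be said is that on the PEGASYS clock no level-driven increase can influence the day 7 to 28 slope or RVR, while on either clock one can influence the decline to week 12.

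The conclusion assumes that Group B priming starts on day -28 as Section 5.3.1 states, and that increases are made within the preferred two weeks. Even if the Section 5.1 schedule gives a single time, Section 7.1 and Appendix 3 would still disagree. The text should be corrected.

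**What to change.** - In Section 7.1, replace the PEGASYS anchor with: *28 days after initiation of ribavirin (Group A study day 28; Group B study day 0, before the first PEGASYS dose)*.
- Use the same wording in Section 8.3.2 and in the pharmacokinetics part of Appendix 5.
- In the virology part of Appendix 5, define day 0 as the day of the first PEG-IFN dose in every arm, and delete the clause tying it to the first dose of study medication.
- Confirm that the Section 5.1 schedule includes a Group B local ribavirin level at the day 0 visit, and add one if it does not.

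The cost is wording changes in three places and at most one extra local aliquot at an existing visit in 35 patients.

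### Group B's ribavirin concentration check has two conflicting dates: study day 0 by the objective, study day 28 by section 7.1

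*Protocol*

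**What the plan says.** The protocol dates the Group B check in two ways.

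- **From ribavirin start.** The primary objective, in the synopsis and in 2.1, places the 2.5 mg/L target "28 days after initiation of ribavirin therapy", and section 3.1 uses the same anchor for Group B. The synopsis regimen for Group B has the concentration "as measured after 28 days after the initiation of ribavirin". Appendix 3 says that if the level is below target "28 days after the initiation of ribavirin, the dose of ribavirin should be increased as soon as possible". The rationale (1.4.1) also expects a concentration after four weeks in the priming arm.
- **From peginterferon start.** Section 7.1, covering Groups A and B together, says "a ribavirin concentration will be obtained at local lab on day 28 after the initiation of PEGASYS".

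Section 8.3.2 and the pharmacokinetics part of Appendix 5 say only day 28 for both groups and name no starting point. Section 5.3.1 shows when Group B's priming begins: that group "will also obtain a plasma sample on day -28", before its first ribavirin dose.

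**The concern.** Concentration targeting is part of what distinguishes Group B from Group C in the primary objective, and the local sample is what sets it in motion. If the sample has two possible dates, so does any dose increase.

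The section 9.3 sample size rests partly on the HCV RNA slope from day 7 to day 28. One timing allows a ribavirin increase before or during that window; the other rules it out. Sites following different sections could also treat patients within the same 35-patient arm differently.

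The central laboratory troughs cannot fill the gap. Appendix 5 has them shipped when the study is complete, so only the local sample can guide dosing.

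**Working it through.** No power or sample size figure is involved. The check is calendar arithmetic on the protocol's own day scale.

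**Inputs**
- Study day 0 is just before the first peginterferon dose (Appendix 5, virology).
- Group B starts ribavirin on study day -28 (5.3.1), which matches the four-week lead-in in 7.1.
- Group A starts both drugs on day 0. Its Appendix 3 footnote reads "Ribavirin concentration measured on treatment day 28".
- If the level is below target, the increase should come preferably within 2 weeks, with a new concentration 4 weeks after the change (8.3.2).
- The second sizing contrast is the slope from day 7 to day 28 (9.3).

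**Group B dates under each rule**

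| Step | From ribavirin start (objective, 3.1, Appendix 3) | From PEGASYS start (7.1) |
|---|---|---|
| Sample, study day | -28 + 28 = 0 | 0 + 28 = 28 |
| Days on ribavirin at sample | 28 | 28 - (-28) = 56 |
| Dose increase, study days | 0 to 0 + 14 = 14 | 28 to 28 + 14 = 42 |
| Recheck, study days | 0 + 28 = 28 to 14 + 28 = 42 | 28 + 28 = 56 to 42 + 28 = 70 |

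The sampling dates differ by 28 - 0 = 28 days. For Group A both rules give day 28, a difference of 0.

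**Against the sizing window (days 7 to 28).** Under the objective's rule the latest increase within the preferred two weeks is day 14, which is 28 - 14 = 14 days before the window closes. Under 7.1 the earliest increase is day 28, the window's last day.

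**Do other sections settle it?** Sections 2.2 and Appendix 5 place day 28 before the fifth peginterferon dose. The unanchored day 28 in 8.3.2 and Appendix 5, read on that calendar, therefore sides with 7.1. Routine ribavirin troughs in 5.3.1 are taken "before the morning dose of ribavirin day 1, day 3, day 7, day, 14, day 28" and later. Group B adds days -27 and -21, and no trough is listed for study day 0. The sampling lists thus lean one way, and the objective, design section and Appendix 3 the other.

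**The case against.** The strongest reply is that little of the regimen actually moves. The lead-in and the 13 mg/kg dose are the same throughout. Only an adjustment moves, and it is at the physician's discretion, depends on tolerance, and is recommended but not mandatory. Section 1.4.1 says ribavirin needs more than four weeks to reach steady state, so an increase on days 0 to 14 would be only partly expressed by day 28. An increase on day 0 itself would require an immediate laboratory result, and two weeks is a preference, not a limit. All of this stands. It limits the likely effect but does not reconcile the two dates.

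Three textual points can also be made.

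- In the objective and 3.1 the 28-day phrase sits in a parenthesis defining the target, so the explicit conflict is mainly between 7.1 and the synopsis regimen and Appendix 3. That is fair, and those places are enough.
- Appendix 5 also describes day 0 as the day study medication is first given, which for Group B could mean ribavirin start. The labels -28, -27 and -21 for the priming phase rule that reading out.
- The 5.1 schedule table is not in the text available for this review and may show which day was intended. No table could make 7.1 agree with the Group B regimen in the synopsis.

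Finally, moving the check to day 0 means that in the section 9.2.1 analysis of SVR by target attainment, a Group B day 28 value could follow a dose increase while Group A's precedes any. That is true. But on study day 28 the two groups already differ in ribavirin exposure, 56 days against 28, so the fix does not create the lack of comparability.

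**Conclusion.** The contradiction is real and confined to Group B: the two rules put the check 28 days apart, and following 7.1 as written departs from the concentration-targeted regimen named in the primary objective. During the day 7 to 28 sizing window it is therefore not settled whether Group B may receive a raised ribavirin dose.

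The day calculations assume priming starts on day -28 and that an increase comes within the preferred two weeks, with no laboratory delay at the early end. No bias is claimed: the protocol gives no basis for estimating how many of the 35 patients would fall below 2.5 mg/L and be adjusted, or what that would do to viral decline. This should be fixed, but it does not undermine the trial.

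**What to change.** In 7.1, 8.3.2 and the pharmacokinetics part of Appendix 5, set the Group B local ribavirin sample at 28 days after the first ribavirin dose, that is study day 0, before the first peginterferon injection. Keep study day 28 for Group A. Confirm that the 5.1 schedule shows the same days.

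Keeping study day 28 for Group B and rewording the rest would also be coherent, but it means changing the primary objective, the synopsis, 3.1, Appendix 3 and the rationale. Aligning the operational sections to the objective is the smaller change. Leave the section 9.2.1 analysis of SVR by target attainment on study day 28, when a central trough is already planned in all arms.

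The cost is amendment wording in three places and one Group B local sample moved from day 28 to day 0. HCV RNA samples already "will be obtained at screening, day 0, day 3, day 7, day 28, week 12", so no visit is added.
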